### Synthesized and Human Emotional Utterances Processing in Autistic Children

This stage of the research aims to edit speech auditory files previously recorded in the first stage in order to synthesize “less natural” voices that would help to approximate a typical emotional processing in autistic children. First of all, naturalness in speech signals will be defined by analyzing standard and neural synthesized voices coming from IBM^®^ Watson text-to-speech system. Their acoustic parameters will be statistically compared to human voice recordings from Stage 1. Analyzed features will cover spectral characteristics, intensity, and duration. Then, frequencies will be filtered, intensity and total duration of speech files will be edited in order to create five types of synthesized voices that correspond to five levels of naturalness: level 1 will be the less natural voice (i.e., approximates standard synthesized voice from IBM^®^ Watson text-to-speech system) and level 5 will be the more natural voice (i.e., approximates human speech). Human and synthesized voices will be further listened and processed by autistic children and matched TD controls while behavioral responses and EEG activity will be registered. Finally, the one synthesized voice processed by autistic participants that will lead to the nearest to human speech EEG processing by controls will be selected for the third stage of the research. The process of Stage 2 is illustrated in Figure 1 and detailed as follows.

**FIGURE 1 F1:**
[figure not shown]
Process of Stage 2. TD, Typically developed.

#### Standard and Neural Speech Files Acquisition

The IBM^®^ Watson text-to-speech system will be used to generate audio files for further analysis. This application proposes a neutral North-American Spanish female voice that will be used in its two versions: standard and enhanced. The former is created by a concatenative synthesis that uses previously recorded speech 10–100 ms segments which represent units that are assembled according to the input text. Discontinuities generated by the process of assemblage lead to a partial degradation of speech naturalness. On the other hand, enhanced or neural synthesized voices are created by Deep Neural Networks able to predict speech acoustic features trained on human speech. This method leads to greater level of naturalness in the output signal (see Baird et al., 2017 for more details about voices synthesis methods). At this stage, neutral words from MESD (MADS corpus) will be entered in the text-to-speech application and their standard and enhanced corresponding audio signals will be downloaded.

#### “Naturalness in Voice” Characterization

Spectral, intensity and duration features (extracted parameters will be the same than the ones extracted in stage 1) of audio signals from standard, neural and human voices will be extracted. As standard and neural synthesized voices are female and neutral, the human adult female voices with neutral prosody will be used for comparisons. A statistical analysis will be carried out to compare those voices and explore tendencies of acoustic characteristics from standard to neural to human voices. One-way ANOVAs will be conducted for voices comparisons on each extracted parameter separately. Normality and homogeneity will be assessed using Shapiro–Wilk and Bartlett tests, respectively. In case of non-parametric distribution of the data, Kruskal–Wallis test will be applied. *Post hoc* comparisons will be conducted to assess specific differences (Tukey procedure in case of ANOVA, Wilcoxon tests with *p*-value adjustment by Holm method in case of Kruskal–Wallis test). Statistical analysis will be performed with R software and level of significance set at *p* < 0.05.

Sample size estimation was calculated with G^∗^Power software version 3.1.9.7 (Faul et al., 2007) for Cohen’s d effect size index of 0.9, statistical significance set at *p* < 0.05. Results indicated that 22 words in each voice type (standard, enhanced, and human) would be enough to provide an estimated power of 0.91. As a result, 24 words per voice type will be used.

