#### Sample

Four healthy male, four healthy female adults (between 19 and 35 years), and eight healthy children (between 9 and 11 years) (Stathopoulos et al., 2011) will voluntary participate to speech recordings. Participants will be excluded if they have been diagnosed with any pathology that affects emotional behavior, hearing, or speech, or present sickness traits affecting voice timbre at the time of the study. Participants will be included if they have grown up in Mexico in a cultural Mexican environment (Mexican academic education and family environments) in order to guarantee a Mexican-way of conveying emotions. Participants will be recruited from a public announcement posted on Tecnologico de Monterrey, Campus Monterrey.

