#### Emotions Classification

Matlab R2019b will be used to carry out a supervised learning analysis using a SVM predictive model on acoustic features extracted from MESD and from INTERACE separately. Hyperparameters will be adjusted to a cubic kernel function and a box constraint level (soft-margin penalty) at 10. The multiclass method (one-vs-one or one-vs-all) and the kernel scale parameters will be set to “auto,” meaning that the algorithm will be automatically optimized for both parameters according to the dataset. The dataset will be divided into two groups: training and validation, corresponding to 77 and 23% of the entire dataset, respectively. A stratified train/test split holdout cross-validation method will be used, so that data training and validation will present an equal number of words per emotion. A dimensionality reduction using Principal Component Analysis, explaining 95% of the variance were applied before classification analysis (Liu et al., 2018).

The following parameters will be computed in order to evaluate the classifier performance (Tharwat, 2020):

-*Accuracy* is the ratio between number of tuples correctly classified and the total number of tuples.-*Precision* represents the relation of the number of correctly classified positive tuples against the total number of tuples classified as positive, including true and false positives. It is an index of exactness of the predictive model.-*Recall* represents the relation of the number of positive tuples correctly classified against the total number of positive tuples, including true positives and false negatives. It is an index of the completeness of the predictive model.-*F-score* is the harmonic mean of precision and recall. It reflects the balance between precision and recall.

A classification analysis will be applied individually on each adult participant and male, and female recordings will analyzed separately. The final dataset of the MESD will be created by selecting for each emotion, the dataset from the participant who the best F-score will be reached. This selection will allow to approximate non-professionalism of actors biases compensation. Classification analysis will be applied on the final 288-utterance dataset of MESD.

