#### Creation of Five Levels of Naturalness for Emotional Speech

Once acoustic features tendencies across naturalness levels will be defined, audio files from emotional human voices recordings will be edited in order to reduce naturalness in those speech signals. Spectral content will be filtered, intensity level and total duration (speech rate) will be adjusted. Acoustic signals edition will be realized using Matlab. For instance, if less naturalness is characterized by higher levels of harmonics-to-noise ratio [human speech is a noisy and continuous signal (Zatorre and Baum, 2012)], then frequencies that are not harmonics will be filtered. The edition of the signal will be applied on previously recorded in Stage 1 audio files for adult male, female, and children voices. Anger, fear, sadness, disgust, happiness, and neutral acoustic signals will be similarly adjusted. Naturalness will be progressively reduced to generate five different levels: from level 1: the less natural to level 5: the more natural voice. Level 1 will correspond to a 95% removal of naturalness, levels 2–5 will correspond to a 76, 57, 38, and 19% diminution, respectively. In accordance with this example, if less naturalness is characterized by higher levels of harmonics-to-noise ratio, then 95% of frequencies that are not harmonics will randomly be filtered for level 1, 76, 57, 38, and 19% of non-harmonics frequencies will be filtered for levels 2–5, respectively. All features defined as being part of naturalness characterization will be edited simultaneously.

Statistical analyses will be used to ensure that levels 1–5 and human voice differ as regard the acoustic parameters edited. Values obtained for each voice and emotion (e.g., adult male/anger, adult female/happiness, etc.) will be analyzed separately with one-way ANOVAs. Normality and homogeneity will be assessed using Shapiro–Wilk and Bartlett tests, respectively. In case of non-parametric distribution of the data, Kruskal–Wallis test will be applied. *Post hoc* comparisons will be conducted to assess specific differences (Tukey after ANOVA, Wilcoxon tests with *p*-value adjustment by Holm method after Kruskal–Wallis). In case of no statistical difference between levels, percentages of diminution of naturalness will be adjusted. Levels must differ for all parameters implicated in naturalness characterization.

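### Naturalness is defined by comparing one synthetic speaker with human female speech, with words as replicates and no speaker term, so the step to human speech cannot be separated from speaker identity

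*Protocol article*

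**What the plan says.** All references are to the Protocol article.

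- *Standard and Neural Speech Files Acquisition*: the synthetic side is a single voice. "This application proposes a neutral North-American Spanish female voice that will be used in its two versions: standard and enhanced". The input text is fixed too: "neutral words from MESD (MADS corpus) will be entered in the text-to-speech application".
- *Naturalness in Voice Characterization*: for the human side, "the human adult female voices with neutral prosody will be used for comparisons". The three voice types are compared by a one-way ANOVA on each parameter (Kruskal–Wallis as fallback, then post hoc tests), to explore tendencies from standard to neural to human. The sample size is counted in words: 22 per voice type for power 0.91 at d = 0.9. Then: "As a result, 24 words per voice type will be used".
- *Sample* (Stage 1): the recordings come from "Four healthy male, four healthy female adults" and eight children.
- *Speech Recordings Elaboration and Procedures*: each adult utters 24 INTERFACE and 24 MADS words per emotion.
- *Emotions Classification*: the final adult database is built by "selecting for each emotion, the dataset from the participant who the best F-score will be reached".
- *Creation of Five Levels of Naturalness for Emotional Speech*: the result is applied to adult male, adult female and child recordings of all prosodies. "All features defined as being part of naturalness characterization will be edited simultaneously".

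**The concern.** Standard and enhanced are two versions of one synthetic speaker. On the human side, 24 neutral MADS words is exactly one woman's list, and the final database keeps one participant per emotion. The most natural reading is therefore one synthetic speaker against one woman.

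Pitch, formants, jitter, shimmer, intensity and rate vary between speakers for reasons unrelated to naturalness. Words from one speaker are repeated measurements on that speaker. Adding words makes it surer that these recordings differ, but says nothing about why.

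The features selected here determine edited levels 1 to 5, which are the Stage 2 EEG stimuli and the source of the Stage 3 synthesized voice. If some of them merely distinguish one synthetic speaker from one woman, the levels are not a pure scale of naturalness. The stated aim of showing that naturalness causes difficulty with emotional prosody would then not be met.

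**Working it through.** **1. The plan's own figure.** Inputs: three voice types, 22 words each (N = 66), d = 0.9, alpha 0.05. With f = d/2 = 0.45, the noncentrality is N·f² = 66 × 0.2025 = 13.365. The power of the F test on 2 and 63 df is 0.902, against 0.91 stated; 23 words would be needed for 0.91. The figure is sound for independent words, and 24 words give 0.927.

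**2. What that calculation leaves out.** Let ρ be the share of a feature's variance that is due to speaker, with total variance 1. The documents give no value, so 0.10 to 0.50 is an assumed range. With no naturalness effect, one synthetic speaker and one woman:

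- Variance of (human mean − mean of both synthetic versions) = 2ρ + (1 − ρ)(1/24 + 1/48) = 2ρ + 0.0625(1 − ρ).
- The ANOVA allows only for 0.0625(1 − ρ).
- At ρ = 0.10: true variance 0.200 + 0.056 = 0.256, allowed 0.056, a ratio of 4.6.
- At ρ = 0.50: true variance 1.000 + 0.031 = 1.031, allowed 0.031, a ratio of 33.

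More words shrink only the second term. With four women the speaker term falls from 2ρ to ρ(1 + 1/4) = 1.25ρ. It does not vanish, because the synthetic side is still one speaker. Equivalently, the design effect 1 + 23ρ reduces 24 words to an effective 24/3.3 = 7.3 at ρ = 0.10 and 24/12.5 = 1.9 at ρ = 0.50. With one speaker on each side, no degrees of freedom remain for between-speaker variance.

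**3. False naturalness rate per feature.** Monte Carlo with at least 20,000 runs per setting, no naturalness effect, both synthetic versions sharing one speaker offset, 24 words per voice type, ANOVA at 0.05:

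| Speaker share (assumed) | 10% | 20% | 30% | 50% |
|---|---|---|---|---|
| One woman, omnibus ANOVA | 30% | 46% | 56% | 70% |
| 24 words over four women (6 each), omnibus | 22% | 34% | 44% | 58% |
| One woman, omnibus plus means ordered standard-enhanced-human | 15% | 22% | 28% | 35% |

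With a speaker share of zero the rate is 5%.

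**4. The proposed rules under the same null.** With all four women at 24 words each:

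- (a) A significant standard-enhanced difference occurs in about 5% of features.
- (c) The standard voice is exchangeable with the four women, so its mean is the lowest or highest of five with probability 2/5 = 40%. This rule would not suffice alone.
- (b) The enhanced value lies on the human side of the standard value about half the time.
- Roughly 0.05 × 0.40 × 0.5 = 1%. Simulation of the three rules jointly gives 1.0% to 1.3% over the same range.

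**5. Single-case t-test.** Comparing the synthetic speaker with four speaker means (3 df) holds about 5%. It needs a gap of 3.18 × √1.25 = 3.6 observed speaker SDs. Its power is about 10%, 24% and 45% for true shifts of 1, 2 and 3 speaker SDs.

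**The case against.** Four points can be made for the plan.

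- **It looks for a gradient.** A reader might infer that every feature that differs is declared part of naturalness. No such rule is written; the plan explores tendencies from standard to neural to human, and the first step lies within one voice. That stands, so 30% to 70% is the rate for an omnibus-only rule. Requiring the order roughly halves it. Also requiring a significant Tukey difference between standard and neural brings it below 1%. But the plan fixes neither requirement.
- **The human side may be several women.** The text says voices, in the plural. A reader might take the comparison of two individual speakers as settled; it is an inference from the word count and the database selection rule. Using four women lowers the error rate but leaves it far above 5%.
- **Rescaling.** *Sound Processing and Analyses* applies max-min rescaling to reduce anatomical differences between individuals. *Naturalness in Voice Characterization* carries over the parameters, but does not say that the rescaling applies. Done within each voice, it would also erase true differences in level.
- **The consequences are limited.** A reader might infer that all stimuli are affected, or that the Stage 3 trial is invalid. Neither follows. The human-voice block is unedited. Group 1 versus Group 2 is randomised and remains a valid comparison of an intervention using edited voice with one using human voice only, whatever the edit is called.

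**Conclusion.** The concern holds for the step from synthetic to human speech. That contrast is confounded with speaker identity, the word is the wrong unit for it, and the stated power of 0.91 does not measure the ability to identify naturalness. Nothing else in the protocol removes the problem.

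The inflation is about 30% to 70% per feature with one woman, 22% to 58% with four women sharing the words, and 15% to 35% with one woman when the ordering is required. These figures rest on an assumed speaker share of 10% to 50% and on the two synthetic versions sharing one speaker offset. If they did not share it, the one-woman omnibus rate would be higher (43% to 89%), and the standard-enhanced contrast would lose its protection.

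The harm is to the meaning of edited levels 1 to 5 and to the conclusion about naturalness. It should be corrected before any edited stimulus is made.

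**What to change.** Amend *Naturalness in Voice Characterization* as follows:

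1. State that the human side is the neutral MADS recordings of all four women from Stage 1 (4 × 24 = 96 words), not only the selected participant, and put speaker in the analysis, for example as a random effect or by averaging each feature per speaker.
2. Count a feature as naturalness only if (a) standard and enhanced differ significantly within the synthetic voice, (b) the enhanced value lies between the standard value and the human mean, and (c) the standard voice lies outside the range of the four women's speaker means.
3. State that the power of 0.91 refers to words within these particular voices.
4. State whether the Stage 1 rescaling applies here and, if so, over which set of recordings the minimum and maximum are taken.

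The single-case t-test with 3 df may be reported as support, but its low power makes it unsuitable as the sole criterion.

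Cost: no new recordings, since all four women already record these words; the change is to the analysis only. The drawback is that fewer features will qualify, because four speakers carry much less information than 24 words appear to.

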#### Creation of Five Levels of Naturalness for Emotional Speech

Once acoustic features tendencies across naturalness levels will be defined, audio files from emotional human voices recordings will be edited in order to reduce naturalness in those speech signals. Spectral content will be filtered, intensity level and total duration (speech rate) will be adjusted. Acoustic signals edition will be realized using Matlab. For instance, if less naturalness is characterized by higher levels of harmonics-to-noise ratio [human speech is a noisy and continuous signal (Zatorre and Baum, 2012)], then frequencies that are not harmonics will be filtered. The edition of the signal will be applied on previously recorded in Stage 1 audio files for adult male, female, and children voices. Anger, fear, sadness, disgust, happiness, and neutral acoustic signals will be similarly adjusted. Naturalness will be progressively reduced to generate five different levels: from level 1: the less natural to level 5: the more natural voice. Level 1 will correspond to a 95% removal of naturalness, levels 2–5 will correspond to a 76, 57, 38, and 19% diminution, respectively. In accordance with this example, if less naturalness is characterized by higher levels of harmonics-to-noise ratio, then 95% of frequencies that are not harmonics will randomly be filtered for level 1, 76, 57, 38, and 19% of non-harmonics frequencies will be filtered for levels 2–5, respectively. All features defined as being part of naturalness characterization will be edited simultaneously.

Statistical analyses will be used to ensure that levels 1–5 and human voice differ as regard the acoustic parameters edited. Values obtained for each voice and emotion (e.g., adult male/anger, adult female/happiness, etc.) will be analyzed separately with one-way ANOVAs. Normality and homogeneity will be assessed using Shapiro–Wilk and Bartlett tests, respectively. In case of non-parametric distribution of the data, Kruskal–Wallis test will be applied. *Post hoc* comparisons will be conducted to assess specific differences (Tukey after ANOVA, Wilcoxon tests with *p*-value adjustment by Holm method after Kruskal–Wallis). In case of no statistical difference between levels, percentages of diminution of naturalness will be adjusted. Levels must differ for all parameters implicated in naturalness characterization.

Sample size estimation was calculated with G^∗^Power software version 3.1.9.7 (Faul et al., 2007) for Cohen’s d effect size index of 0.9, statistical significance set at *p* < 0.05. Results indicated that 17 words in each level would be enough to provide an estimated power of 0.92.

As all emotions will be edited similarly, relations between emotions will be preserved [e.g., stage 1 would highlight that harmonics-to-noise ratio for happiness > harmonics-to-noise ratio for sadness (Scherer et al., 2011)]. Therefore, the differentiation between emotions will not be affected by editing the level of naturalness of the voice. However, statistical analyses will be applied to verify this assumption after voices synthesis. For comparisons between emotions, values obtained for acoustic features listed in stage 1 will be analyzed for each voice separately with one-way ANOVAs. Normality and homogeneity will be assessed using Shapiro-Wilk and Bartlett tests, respectively. In case of non-parametric distribution of the data, Kruskal-Wallis test will be applied. Post-hoc comparisons will be conducted to assess specific differences (Tukey after ANOVA, Wilcoxon tests with *p*-value adjustment by Holm method after Kruskal–Wallis).

Sample size estimation was calculated with G^∗^Power software version 3.1.9.7 (Faul et al., 2007) for Cohen’s d effect size index of 0.8, statistical significance set at *p* < 0.05. Results indicated that 19 words in each emotion would be enough to provide an estimated power of 0.92.

In all cases, statistical analysis will be performed with R software and level of significance will be set at *p* < 0.05.

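### The check that the naturalness levels differ treats versions of the same utterances as independent samples, so it can reject levels that differ within every utterance, and its stated power is for a different test

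*Protocol article*

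**What the plan says.** All of this is in the Protocol article, section Creation of Five Levels of Naturalness for Emotional Speech.

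- Source of the stimuli: "The edition of the signal will be applied on previously recorded in Stage 1 audio files for adult male, female, and children voices".
- Edit steps: "Level 1 will correspond to a 95% removal of naturalness, levels 2–5 will correspond to a 76, 57, 38, and 19% diminution, respectively".
- Purpose of the check: "Statistical analyses will be used to ensure that levels 1–5 and human voice differ as regard the acoustic parameters edited".
- Test: "Values obtained for each voice and emotion (e.g., adult male/anger, adult female/happiness, etc.) will be analyzed separately with one-way ANOVAs". Post hoc tests are Tukey after ANOVA, or Holm-adjusted Wilcoxon tests after Kruskal–Wallis. No utterance factor is named.
- Acceptance rule: "Levels must differ for all parameters implicated in naturalness characterization".
- Action on failure: "In case of no statistical difference between levels, percentages of diminution of naturalness will be adjusted".
- Sizing, for d = 0.9 and a 0.05 level: "Results indicated that 17 words in each level would be enough to provide an estimated power of 0.92". No correlation between versions is entered.

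**The concern.** The six conditions are matched by utterance. A one-way ANOVA or a Kruskal–Wallis test ignores the matching and judges the edit effect against the spread between different words. That spread is irrelevant to whether the edit changed the signal.

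This does not look like a shortening of the text for publication. The same article specifies repeated-measures ANOVAs for the culture comparison (Sound Processing and Analyses) and for the EEG data (Stage 2, Statistical analysis). It also enters a repeated-measures correlation of 0.5 for the EEG sample size (Stage 2, Participants).

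The check decides whether the Stage 2 stimuli are accepted or re-edited. A test that is too insensitive can send levels that are already distinct back for re-editing, and the stated power gives no warning of this.

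**Working it through.** **1. The plan's own figure.** Take f = d/2 = 0.45 and independent groups, with noncentrality λ = f² × N.
- Five groups of 17: λ = 0.2025 × 85 = 17.2, power 0.916. This reproduces 0.92.
- Six groups of 17 (levels 1–5 plus human): λ = 0.2025 × 102 = 20.7, power 0.947. This does not.

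The 0.92 is therefore the power of one omnibus test on five independent groups. The check compares six matched conditions, which form 6 × 5 / 2 = 15 pairs.

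**2. What the pairwise rule needs as written.** Tukey calls two conditions different when their observed means differ by at least q(0.95; 6, 6(n−1)) / √n, in units of the between-utterance SD. The number of words used in this check is not stated. The final corpus has 48 per emotion, 24 from each source, so 17, 24 and 48 are all shown.

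| Words n | q | Gap needed (SD) | Human to level 1, five gaps (SD) |
|---|---|---|---|
| 17 | 4.11 | 1.00 | 4.99 |
| 24 | 4.09 | 0.83 | 4.17 |
| 48 | 4.06 | 0.59 | 2.93 |

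**3. What the planning effect implies.** If d = 0.9 is the full range, each of the five steps is 0.18 SD. If f = 0.45 with even spacing over six conditions, the range is 2 × 0.45 × √(15/7) = 1.32 SD, or 0.26 SD per step. Both are far below the gaps in the table.

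**4. What pairing changes.** The standard error of a difference between two versions falls by a factor √(1−ρ), where ρ is the within-utterance correlation: 0.71 at ρ = 0.5, 0.32 at 0.9 and 0.10 at 0.99. The documents do not give ρ, so these values are assumptions.

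**5. Simulated chance that all 15 pairs differ in one voice-by-emotion cell** (normal data, equal steps):

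| Words | Step (SD) | ρ | Tukey as written | Paired, Holm |
|---|---|---|---|---|
| 17 / 24 / 48 | 0.26 | 0.90 | 0.00 / 0.00 / 0.00 | 0.02 / 0.19 / 0.90 |
| 17 / 24 / 48 | 0.26 | 0.99 | 0.00 / 0.00 / 0.00 | 1.00 / 1.00 / 1.00 |
| 24 | 0.40 | 0.90 | 0.00 | about 0.95 |
| 24 | 0.60 | 0.50 | 0.00 | 0.22 |
| 17 / 24 / 48 | 0.90 | 0.90 | 0.09 / 0.38 / 1.00 | 1.00 / 1.00 / 1.00 |
| 24 | 1.20 | 0.90 | 0.98 | 1.00 |

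At a step of 0.18 SD the Tukey column is also 0.00 for every n.

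**6. Levels that differ in every utterance.** With n = 17, a step of 0.45 SD and ρ = 0.99, all six versions are strictly ordered within every utterance in 94% of simulated data sets. The all-pairs Tukey check passes in 0% and the paired check in 100%.

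**7. The protocol's harmonics-to-noise example.** Assume noise energy falls in proportion to the frequencies removed. The gain is then −10 log₁₀(1 − fraction removed): 0.92, 2.08, 3.67, 6.20 and 13.01 dB for levels 5 to 1. The smallest step, human to level 5, reaches the Tukey gap only if the between-utterance SD is below about 0.92, 1.10 or 1.56 dB at 17, 24 or 48 words. At an assumed SD of 2 dB the check as written passes 0.00, 0.00 and 0.03, and the paired check 1.00 throughout.

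**The case against.** A reader might infer that distinct levels will always fail, or that the rule cannot in practice be met. The documents do not support that. It depends on step size relative to between-utterance SD, which they do not give, and the table shows the unpaired rule being met at large steps.

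A reader might also infer that changing the percentages cannot help, since the steps are already an equal 19 points. That holds only for a roughly linear response. In the log-scale harmonics-to-noise example, respacing to equal steps of 13.01 / 5 = 2.6 dB passes 1.00 at SD 2 dB with 24 or 48 words. The scope is still limited: the steps already use 95 of 100 points, and all features are edited together.

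Three further objections carry weight.
- The plan never says that every pair must differ. If only the omnibus test counts, the rule is easy to meet. The post hoc tests, followed directly by the sentence about no difference between levels, favour the pairwise reading, but it remains an inference.
- Pairing is not the whole story. With small steps or low ρ the paired check also fails often, because requiring every pair is demanding in itself.
- The error is conservative. It leads to re-editing, not to accepting indistinct levels or stopping the study. A paired test has the opposite weakness: tiny imposed edits can be significant.

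What stands regardless is that the test does not fit matched data and that 0.92 does not describe the check.

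**Conclusion.** The point holds in a limited form. That the conditions are matched and the tests are not follows from the text alone. That 0.92 is a five-group independent omnibus figure follows from reproducing it (0.916).

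The consequence is that the check can reject levels that are consistently distinct within utterance. On the pairwise reading, the simulated pass rate is 0.00 at the planned effect size for 17, 24 and 48 words. It reaches 0.98 per cell at steps of 1.2 SD with 24 words, and about 1.00 at 0.9 SD with 48. How often needless re-editing would occur cannot be fixed from the documents. The simulated rates assume normal data, equal steps and ρ between 0.5 and 0.99.

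This should be corrected because the check governs the Stage 2 stimuli and the correction is cheap. It does not show that the stimuli cannot be built.

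**What to change.** 1. Replace the one-way ANOVA with a within-utterance analysis: repeated-measures ANOVA, or a mixed model with utterance as a random effect. The non-parametric fallback becomes a Friedman test with paired Wilcoxon tests.
2. State the rule explicitly. Require Holm-adjusted paired significance for the five adjacent contrasts: human–5, 5–4, 4–3, 3–2 and 2–1. With ordered levels, the wider pairs normally have the smaller p-values. The last five Holm steps over 15 pairs then use the same thresholds (0.05/5 to 0.05/1) as Holm over the five adjacent contrasts, so the paired column above applies to this rule too.
3. Report the size of each step, so that significant but trivially small steps are visible.
4. Restate 17 words and 0.92 as a five-group omnibus figure, and give the power for the paired adjacent contrasts under a stated correlation.

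The cost is a few lines of analysis text and one power calculation, with no new recordings.

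### The check that editing leaves emotion differences intact tests each voice on its own, so it shows that some difference remains, not that it matches the human voice

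*Protocol article*

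**What the plan says.** The section *Creation of Five Levels of Naturalness for Emotional Speech* argues that all emotions are edited alike, so their relations are kept, and concludes that "the differentiation between emotions will not be affected by editing the level of naturalness of the voice". It then adds: "However, statistical analyses will be applied to verify this assumption after voices synthesis". The analysis given for this is that "values obtained for acoustic features listed in stage 1 will be analyzed for each voice separately with one-way ANOVAs", with Kruskal–Wallis as the fallback and Tukey or Holm-adjusted Wilcoxon tests afterwards.

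The check has its own sample size statement, "for Cohen’s d effect size index of 0.8" at the 0.05 level: "Results indicated that 19 words in each emotion would be enough to provide an estimated power of 0.92".

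The other analysis in that section compares the levels and the human voice within each voice and emotion. Its aim is to show that the levels differ on the edited parameters. It does not ask whether the emotion contrasts are kept.

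**The concern.** The statement to be verified is about change: the emotion differences after editing should equal those before it. Statistically, that is an absence of Emotion × Level interaction. The planned ANOVA has a different null, that all six emotions have equal means within one voice. Rejecting it shows that not all differentiation has gone. It does not show how much of the human-voice differentiation is left. A significant result in the human voice and another in an edited voice do not show that the two effects are equal, and a significant result beside a non-significant one does not show that they differ.

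This matters because the Stage 2 ERP analysis of deviants uses emotional-minus-neutral difference waves. The protocol's section *EEG Signature of Emotion Recognition* describes MMN amplitude as reflecting discrimination of acoustic change. If editing weakens the acoustic contrast between emotional and neutral words, an ERP change across levels could come from weaker emotional cues, from reduced naturalness, or from both. The check is the safeguard against that confusion. The Discussion would read an absence of any naturalness effect as evidence that the edited parameters play no part in autistic impairments, and undetected loss of contrast would undermine that reading too.

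**Working it through.** **Inputs from the protocol.** There are six emotion categories (anger, fear, sadness, disgust, happiness, neutral). The effect size is d = 0.8, alpha is 0.05, and 19 words per emotion are stated to be enough. *MESD Speech Corpus Stimuli* gives 48 words per emotion in the final corpus, 24 from each source.

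**Formula.** For a one-way ANOVA with k = 6 groups of n words, N = 6n, the degrees of freedom are 5 and N − 6, and power is the upper tail of a noncentral F with λ = f² × N.

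**Reproducing the stated power.** Take f = d/2 = 0.4 and n = 19. Then N = 114 and λ = 0.16 × 114 = 18.24, which gives power 0.916 against the stated 0.92. Other readings of d = 0.8 do not reproduce it: f = d√(1/(2k)) gives 0.42, f = 0.8 gives more than 0.999, and a two-group comparison gives 0.69. The check is therefore sized to detect any difference among six emotions within one voice.

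**If editing halves every emotion difference** while within-emotion spread stays the same, f falls from 0.4 to 0.2:

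| Words per emotion | N | λ = 0.04 × N | Still significant after halving | Significant if intact (f = 0.4) |
|---|---|---|---|---|
| 19 | 114 | 4.56 | 32% | 92% |
| 24 | 144 | 5.76 | 40% | 97% |
| 48 | 288 | 11.52 | 74% | >99% |

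With 48 words, an effect of f = 0.213 is still significant with 80% probability. That is 0.213/0.4 = 53% of the design effect.

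**Larger human-voice effects (assumed; not in the protocol).** After halving, the ANOVA is still significant as follows:
- from f = 0.6: 79% with 24 words and 98.6% with 48;
- from f = 0.8: 97% with 24 words and about 100% with 48.

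The result thus depends on the number of words and the starting effect, and not on the fraction lost.

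**A paired comparison for contrast.** Pair each edited file with its human source and test Emotion on the within-word change. In simulation (equally spaced emotion means, spread unchanged by editing), this detects a halving from f = 0.4 in 40–84% of runs with 24 words and 74–99% with 48. The ranges correspond to assumed within-word correlations of 0.5 to 0.8.

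**The case against.** Four points can be made for the plan.

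1. **Post hoc tests are planned.** The same emotion comparison is made on the human recordings in Stage 1, so the pairwise results can be set side by side. In simulation with equally spaced emotions, halving cuts the mean number of Tukey-significant pairs (of 15) from about 6.4 to 1.6 at f = 0.4 with 48 words. A drop of that size would be visible. This stands as description. It is not a test, because single pairs also drop out by chance in about half or more of runs when nothing is lost.

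2. **The check need not pass when half the contrast is gone.** A reader might infer that it almost always would. At the protocol's own f = 0.4 that is not so: with 19 or 24 words the ANOVA more often turns non-significant. Near-certain passing needs larger human-voice effects, which are an assumption.

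3. **No pass rule is stated.** A reader might infer that a weakened level would be recorded as verified. The article does not say what counts as verified, and a condensed article may leave that to the full protocol. The criticism is of the test that the article does fix.

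4. **Voice selection may be partly protected.** A reader might infer that a voice with weakened emotion would go forward to Stage 3. The voice is chosen by closeness of MMN to that of controls hearing human voices, and the protocol expects smaller ERPs in autistic children. Weaker contrast would tend to reduce MMN further, which works against choosing that voice. The confusion in the level comparisons remains.

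None of these supplies a comparison of edited with human emotion differences.

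**Conclusion.** The concern holds in this form: the article names a claim about change and fixes a test that does not address change. This is a wrong analysis for the stated aim, not a detail left to another document. The protocol already uses factorial models for comparable questions in *Sound Processing and Analyses* (Corpus × Emotions, and Cultures × Emotions with repeated measures).

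The size is 74% still significant after a halving at 48 words per emotion, 40% at 24 and 32% at 19. These figures rest on f = 0.4, recovered from the protocol's power statement, and on within-emotion spread being unchanged by editing. The range of 79–100% applies only if human-voice effects are f = 0.6–0.8 with 24–48 words. The documents support possible mixing of contrast loss with naturalness in Stage 2. They do not show that editing will compress the contrasts, nor that a weakened voice would be selected.

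**What to change.** For each acoustic feature, fit Emotion × Level with the source recording as the repeated unit, so that each edited file is paired with its human original. For each level, report the overall between-emotion effect, standardised by within-emotion spread, as a ratio to that in the human voice with a 95% CI. Keep the per-voice ANOVAs and post hoc tests as description.

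Three cautions apply:
- **Standardise.** If editing halves a feature's means and spread alike, f is unchanged. A test on raw edited-minus-human change would still flag a loss, in 91–100% of simulated runs at f = 0.6–0.8.
- **Do not read a non-significant interaction as proof of preservation.** The interval is the evidence.
- **State any acceptance margin beforehand, for the overall effect and not for each pair**, and check its chance of accepting a truly preserved level. A lower bound above 0.8 required of each pair would be too strict. At f = 0.4 with 48 words and nothing lost, it accepts the largest contrast in only 24–48% of runs and adjacent emotions in about 5%.

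The cost is a little more analysis on files that will exist anyway. Some levels may need re-editing before EEG recording; the section already allows the percentages to be adjusted when levels do not differ.
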